### **9.3 Statistical methods**

#### **9.3.1 General considerations**

The quantitative variables will be described by the following parameters: number of patients, number of missing values, mean, standard deviation (SD), median, first and third quartiles (Q1 and Q3), minimum and maximum. Categories could be defined if applicable using a cut-off threshold from literature or quantiles.

The qualitative variables will be described by the following parameters: number of patients, number of missing values, frequency and percentage of each modality (missing values will not be included in the denominator used for frequency computation).

The analyses will be performed using the R and SAS software. They will be performed by the biostatistics unit of the University of Milano-Bicocca.

After the end of the statistical analysis of the DOWN-SUITE study, a meta-analysis could be carried out with the French partner ([name], Hospices Civils de Lyon), who applied for funding for a similar study (DOWN-SUITE-Fr, the result of which is pending).

#### **9.3.2 Primary endpoint**

The analysis of the primary endpoint will be performed by a mixed effects logistic regression model. It will take into account as explanatory variables the group of intervention, as well as the stratification factors (the site as random effects and the baseline NIHSS score [dichotomised 0 to 5 versus 6 or more] as fixed effect). The effect of the intervention on the occurrence of good collaterals will be assessed by a Wald test and quantified through the adjusted odds ratio with the associated 95% confidence interval.

The agreement between readers will be estimated using the Cohen's kappa or the weighted Cohen's kappa coefficient for the dichotomised ASITN/SIR collateral score (good collaterals: score 3 to 4; poor collaterals: score 0 to 2) and the ASITN/SIR collateral ordinal score,

respectively. Coefficients of  $\leq 0.20$ , 0.21-0.40, 0.41-0.60, 0.61-0.80 and  $> 0.80$  indicate poor, fair, moderate, good and excellent agreement, respectively.

A pre-planned secondary analysis will evaluate the effect of HOB positioning on the primary endpoint (ASITN/SIR collateral score, grade 3–4) across all patients, treating HOB angle as a continuous variable calculated as a time-weighted average (integrating angle and duration per patient to account for within-patient variations, including HDT15 patients requiring standard positioning due to intolerance). In particular, for each patient, the time-weighted average lower HOB exposure” will be calculated as follows, with higher values representing greater exposure to lower head positions:

$$\text{time-weighted lower HOB exposure} = \left( \sum \frac{(30^\circ - \text{HOB angle} + 1) \times \text{duration}}{\text{total duration}} \right)$$

This analysis will use a mixed-effects logistic regression model, adjusted for stratification factors (site as random effect, baseline NIHSS [0–5 vs.  $\geq 6$ ] as fixed effect) and covariates (baseline collateral status on vascular neuroimaging at admission; intravenous rt-PA treatment), reporting adjusted odds ratios with 95% confidence intervals.

Pre-specified sensitivity analyses will include: (1) per-protocol vs. modified intention-to-treat analysis; (2) inclusion of only those patients with baseline NIHSS  $\geq 6$ ; (3) exclusion of HDT15 patients with tilting duration  $< 50\%$  of the time from randomization to angiographic collateral assessment; and (4) comparison of control arm subgroups ( $0^\circ$  to  $+5^\circ$  vs.  $+6^\circ$  to  $+30^\circ$ ) to HDT15. The number of patients achieving complete or partial recanalization (spontaneous or rt-PA-induced) at the first angiographic assessment during MT will be reported for both arms.

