#### 4.2 Method for randomisation

Central randomisation will be performed by an online, secure, software application (Sealed Envelope; <https://www.sealedenvelope.com>). The group of intervention will be automatically assigned following a pre-established randomisation list completed by the statistician of the study. The allocation ratio between the HDT15 (intervention) and usual position (control) groups will be 1:1. Randomisation will be stratified by site. To take into account the inter-individual heterogeneity in baseline collateral status, randomisation will also be stratified according to score of the National Institute of Health stroke scale (NIHSS) at presentation in the Emergency Room (dichotomised 0 to 5 versus 6 or more), which will be assessed before treatment allocation. Patients with NIHSS 0 to 5 will be considered as having a “minor stroke” despite a M1 occlusion, which will be considered as a surrogate marker of good baseline collaterals.

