## **9 STATISTICAL ASPECTS**

### **9.1 Number of subjects needed**

Considering previous data on distribution of acute stroke patients across the ASITN/SIR collateral scale, a sample size of 118 patients (59 patients per group) should yield 80% power to detect a between group difference of 25% (60% in experimental group versus 35% in control group) for the primary endpoint, which is considered of substantial clinical significance, with a bilateral alpha risk of 0.05.

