In order to strictly follow the ASITN/SIR grading recommendations (detailed above), the acquisition parameters of the angiography runs for assessing the primary endpoint will be

specified and homogenised across all recruiting centers (anterior and lateral field of view, frame rate, inclusion of arterial and late venous phases).

The Central Imaging Core Lab will also evaluate the baseline neuroimaging and determine the pretreatment collateral status of all patients, using a dichotomised version of the criteria reported by Tan et al. (collateral supply filling 0% to 50% versus 50% to 100% of the occluded MCA territory).

Two independent experts (Interventional Neuroradiologists), blind to treatment allocation and not involved in patient recruitment will independently grade all patients, thus allowing for the evaluation of inter-rater reproducibility. All discrepant cases will be resolved by a third independent expert, also blind to treatment allocation.

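### The primary model is valid but inefficient: it adjusts for an NIHSS surrogate and leaves out the core-lab baseline collateral status that the trial already collects

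*Protocol*

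**What the plan says.** Section 9.3.2 sets the primary analysis as a mixed-effects logistic regression. On its content it says: "It will take into account as explanatory variables the group of intervention, as well as the stratification factors", with site as a random effect and dichotomised NIHSS as a fixed effect. The treatment effect is tested by a Wald test and reported as an adjusted odds ratio.

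Section 4.2 explains why NIHSS is a stratification factor. It is there to deal with differences between patients in baseline collaterals, and an NIHSS of 0 to 5 is something "which will be considered as a surrogate marker of good baseline collaterals".

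Section 10.2 also obtains the direct measure. From the baseline neuroimaging the core lab will "determine the pretreatment collateral status of all patients", in two categories split at 50% filling of the occluded territory.

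That measure enters one model only, the secondary head-position exposure analysis in 9.3.2, which adjusts for "covariates (baseline collateral status on vascular neuroimaging at admission; intravenous rt-PA treatment". None of the four sensitivity analyses at the end of 9.3.2 adds it to the comparison of randomised groups.

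**The concern.** The endpoint is a collateral grade taken after positioning, so a collateral grade taken before positioning is the natural covariate. The protocol treats baseline collaterals as the heterogeneity that matters, measures them, and then puts only a coarse clinical proxy into the main test.

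Two things are at stake. One is power, in a trial sized at 80% without an allowance for the patients whom 4.3.1 and 9.2 remove because the vessel has already reopened. The other is chance imbalance between arms in baseline collaterals, which the planned model corrects only as far as NIHSS reflects it.

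**Working it through.** **1. The plan's own figure.** Section 9.1 states that "a sample size of 118 patients (59 patients per group) should yield 80% power" for a "between group difference of 25% (60% in experimental group versus 35% in control group", "with a bilateral alpha risk of 0.05". With unpooled variance:

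n per group = (z0.975 + z0.80)² × [p1(1−p1) + p2(1−p2)] / (p2−p1)²

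= (1.960 + 0.842)² × (0.35×0.65 + 0.60×0.40) / 0.25² = 7.849 × 0.4675 / 0.0625 = 58.7, so 59.

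The stated size reproduces. The pooled formula gives 62 per group, and 78.4% power at 59. Neither calculation takes credit for covariates.

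**2. Is the variable a legitimate baseline covariate?** Sections 5.5 and 6.1.1 place vascular imaging before randomisation and the start of tilting after it. Section 10.2 has the readers blind to allocation. Tilting therefore cannot affect the covariate, and adjusting for it brings in no post-randomisation bias.

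**3. Power with and without it.** Simulated trials of 118 patients (1:1), 8,000 per row, with marginal rates held at 35% and 60% (or 35% in both arms for type I error).

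Assumptions that are not in the documents:
- 50% of patients have good baseline collaterals.
- 15% have NIHSS 0 to 5 (22.5% of those with good and 7.5% of those with poor collaterals).
- NIHSS 0 to 5 has an odds ratio of 1.5 for the endpoint.
- There is no site effect.

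Both models contain treatment and NIHSS; the second adds baseline status.

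| Assumed OR, baseline status to endpoint | Power, NIHSS only | Power, baseline added | Gain (points) | Median treatment OR, without / with | Type I error, without / with |
|---|---|---|---|---|---|
| 1 | 79.2% | 79.0% | −0.2 | 2.86 / 2.90 | 4.8% / 4.9% |
| 2 | 78.4% | 79.3% | 0.9 | 2.86 / 2.98 | 4.9% / 4.9% |
| 4 | 78.4% | 82.1% | 3.7 | 2.89 / 3.30 | 4.8% / 4.9% |
| 6 | 79.3% | 85.6% | 6.3 | 2.92 / 3.67 | 4.5% / 5.1% |
| 10 | 78.6% | 88.3% | 9.7 | 2.91 / 4.24 | 4.8% / 4.6% |

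The simulation standard error of each power figure is √(0.79×0.21/8000), about 0.5 point. Further runs with NIHSS in both models gave about 2 points at OR 3, 4 to 5 at OR 4 to 5, and 9 at OR 10.

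**4. Sensitivity to the other assumptions.**
- 30% or 70% good at baseline: at OR 4, power goes from 78.7% to 82.2% and from 78.3% to 81.8%; at OR 10, from 79.0% to 86.7% and from 78.9% to 85.7%.
- NIHSS odds ratio of 3, with 5% to 25% of patients at NIHSS 0 to 5: the gain is about 3 points at OR 4 and 9 to 10 at OR 10.

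**5. Unreadable baseline scans.** Section 9.5 rules out imputation, so a model that needs the covariate would drop patients without it. Adjusted power in such a complete-case fit (10,000 trials per cell):

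| Patients left of 118 | OR 4 | OR 10 |
|---|---|---|
| 118 | 82.9% | 88.4% |
| 112 (5% lost) | 80.8% | 86.7% |
| 106 (10% lost) | 79.2% | 84.2% |
| 94 (20% lost) | 73.5% | 79.8% |

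In the same runs, NIHSS-only power with all 118 patients was about 79%. At OR 4 the gain is gone at about 10% loss, and at OR 10 at about 20%. Keeping 10% of patients in a separate unreadable category preserved most of the gain.

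**6. Chance imbalance.** With 50% prevalence, the standard error of the between-arm difference in baseline status is √(0.25×2/59) = 0.092. An imbalance of 10 points or more has z = 0.10/0.092 = 1.09, or about 28% of trials (ignoring stratification). At OR 5 the endpoint rate differs by about 35 points between baseline categories, so such an imbalance moves the crude difference by about 0.10 × 35 = 3.5 points, against a planned 25.

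**The case against.** The best defence is that nothing here is wrong. A randomised comparison adjusted for its stratification factors is standard, its type I error is intact, and the sample size never relied on further covariates. That stands.

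A reader might infer that the analysis is invalid, or that the omission takes power below the planned level. The documents support neither: NIHSS-only power is about 78% to 79% in the table, in line with section 9.1.

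A reader might also see a contradiction between the two covariate sets in 9.3.2. There is none. The head-position model compares exposures that were not randomised and needs control of confounding; the primary model does not.

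The second objection is that the gain rests on an assumption. No section gives an association between admission collateral status and the angiographic grade. It could be modest: the covariate is a two-level split read from CT or MRI, and the endpoint is a dynamic grade taken later by another method. This also stands. A gain of 5 to 10 points needs an odds ratio of about 5 or more and should not be quoted as expected.

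Third, the gain is not automatically free. Ungradable scans could erase it under a complete-case fit (step 5), so the change needs a rule for them.

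Two smaller points also have weight. Section 9.4 allows the sample size to be reassessed, so the trial is not wholly without recourse. A difference in proportions beside the odds ratio is a reporting addition that could be left to the analysis plan.

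What the defence does not answer is the protocol's own reasoning. Section 4.2 singles out baseline collaterals as the heterogeneity to control, and 9.3.2 then names a closed covariate list without the direct measure.

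**Conclusion.** The point holds as one of efficiency. The primary model is valid, but it relies on a surrogate for a variable that the trial measures directly, before randomisation and with blinded readers.

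At 59 per arm, adding that variable is worth about 0 to 1 point of power at an odds ratio of 1 to 2, about 2 at 3, about 4 to 5 at 4 to 5, and about 9 at 10. Type I error stays at about 5%. In no setting did the addition lower power beyond simulation error, provided that no patient is dropped.

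These figures rest on the assumed association, prevalence and NIHSS effect, and on leaving out site effects. The rationale in 4.2 makes a very weak association unlikely but does not establish a strong one. This is a recommended improvement at low cost, not the repair of an error.

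**What to change.** In section 9.3.2, add the dichotomised core-lab pretreatment collateral status as a fixed effect in the primary model. Keep site and NIHSS as they are; the new term joins them and does not replace NIHSS. Give the covariate a third category for unreadable or missing baseline imaging, so that every patient with an assessed endpoint stays in the model under section 9.5. State which category takes exactly 50% filling, since 10.2 lists it in both.

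Fix the change before unblinding, including any comparison of arms at the interim analysis in 9.4. The documents do not show whether that analysis has taken place. If it has, the amendment should record who had seen results by arm when the covariate was chosen.

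The cost is one model term and one rule; no new data are needed, because 10.2 already plans the grading for all patients. The downside is interpretive: the treatment odds ratio becomes conditional on the covariate and lies further from 1 (for example 3.30 against 2.89 at OR 4), so it must be labelled as conditional. Optionally, report a covariate-standardised difference in proportions with its 95% confidence interval beside it, so that the result can be read against the planned 25 points.

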### **5.4 Criteria for discontinuation of study procedure**

HDT15 will be discontinued in cases of patient-reported intolerable discomfort, observed severe discomfort in non-communicative patients, or at the treating physician's discretion for clinical reasons (e.g., vomiting). All reasons for discontinuation will be recorded and reported as safety data.

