#### ii. safety outcomes:

- Mean values of systolic blood pressure, diastolic blood pressure and oxygen saturation at entry in the Emergency Room, at entry in the angio suite and every 15 minutes from the start to the end of MT; they will be treated as continuous variables and calculated as mean with their 95% confidence interval for each group.
- Proportion of patients presenting one or more episodes of vomiting from randomisation to the completion of MT will be calculated with their 95% confidence interval for each group.
- Reasons for HDT15 discontinuation (e.g., intolerable discomfort, observed severe discomfort in non-communicative patients, vomiting, neurological worsening,

headache, or respiratory distress), minor adverse events, and MT-related technical challenges will be recorded and reported as proportions with 95% confidence intervals.

- The proportions of patients who had an increase of  $\geq 4$  points on the NIHSS score within  $24 \pm 12$  hours of the randomisation will be calculated with their 95% confidence interval for each group.
- The proportions of patients who had SICH within  $24 \pm 12$  hours will be calculated with their 95% confidence interval for each group.
- The proportions of patients with pneumonia within the first 72 hours after randomisation will be calculated with their 95% confidence interval for each group.
- Safety data, including serious and non-serious adverse events, as well as reasons for HDT15 discontinuation (e.g. discomfort, vomiting, neurological worsening, headache, respiratory distress) and technical challenges related to MT will be reported for both treatment arms. Adverse events will be categorized according to the Medical Dictionary for Regulatory Activities (MedDRA) v28.0.

iii. **efficacy** outcomes:

- functional outcome at 3 months, assessed with the ordinal score on the modified Rankin scale (shift across outcomes on the mRS between groups).
- Percent change in NIHSS ( $[(\text{Admission NIHSS} - \text{time-point NIHSS}) \times 100 / \text{Admission NIHSS}]$ ) from admission to immediately pre-MT, at  $24 \pm 12$  hours, and at  $7 \pm 2$  days (or discharge), calculated with 95% confidence intervals.

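### Sensitivity analysis (3) of the primary endpoint removes poorly adherent patients from the HDT15 arm only, so it cannot test the robustness of the modified intention-to-treat result

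*Protocol*

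**What the plan says.** Protocol section 9.2 sets the main analysis on a modified intention-to-treat (mITT) basis: patients already recanalised at the first angiogram are left out, by the same rule in both arms. Section 9.3.2 compares the arms by mixed-effects logistic regression with site and NIHSS stratum.

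Section 9.3.2 then lists four sensitivity analyses. The third is the "exclusion of HDT15 patients with tilting duration" shorter than half of the interval between randomisation and the angiographic collateral assessment. No matching rule is given for controls.

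On why tilt may stop, section 5.4 says: "HDT15 will be discontinued in cases of patient-reported intolerable discomfort, observed severe discomfort in non-communicative patients, or at the treating physician's discretion for clinical reasons". Section 9.3.3 will report "reasons for HDT15 discontinuation (e.g. discomfort, vomiting, neurological worsening, headache, respiratory distress" among the safety data. On the link between severity and collaterals, section 4.2 treats an NIHSS of 0 to 5 at presentation as a minor stroke, "which will be considered as a surrogate marker of good baseline collaterals".

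Section 9.3.2 also plans a time-weighted head-position analysis. It keeps all patients, including HDT15 patients returned to standard positioning, and adjusts for baseline collateral status and rt-PA.

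**The concern.** A sensitivity analysis of the primary result should ask the same question under different assumptions. Item (3) changes who is compared. Whether a patient reaches 50% tilt is known only after randomisation, in a window that closes at the primary endpoint reading, and the rule applies to one arm. HDT15 patients who could stay tilted are set against all controls, including those who would not have tolerated the position.

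If the removed patients differ from the rest in collateral status, the contrast moves even when HDT15 does nothing. Agreement with a positive mITT result could then be false reassurance. A positive item (3) beside a null mITT result would invite the claim that HDT15 works when it is maintained. A shift the other way could wrongly cast doubt on a real effect.

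**Working it through.** **Inputs from Protocol 9.1.** "a sample size of 118 patients (59 patients per group"), rates of "60% in experimental group versus 35% in control group", "with a bilateral alpha risk of 0.05", and 80% power.

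**The plan's own figure.** With the unpooled normal approximation, n per arm = (1.960 + 0.842)² × (0.60×0.40 + 0.35×0.65) / 0.25² = 7.849 × 0.4675 / 0.0625 = 58.7, rounded up to 59. The stated size reproduces and is not at issue.

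**Assumptions.** The protocol gives neither the share f of HDT15 patients tilted for under 50% of the window nor their good-collateral rate g. Both are varied.

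**Bias when HDT15 has no effect.** Both arms have a true rate of 35%. After removal, the HDT15 rate is (0.35 − f×g)/(1 − f), while the control rate stays at 0.35.

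- f = 10%, g = 10%: (0.35 − 0.01)/0.90 = 0.378, or +2.8 points.
- f = 20%, g = 10%: (0.35 − 0.02)/0.80 = 0.4125, or +6.25 points (about 6.3), a quarter of the planned 25-point difference.
- g = 35%, any f: 0 points.
- f = 10%, g = 50%: (0.35 − 0.05)/0.90 = 0.333, or −1.7 points.
- f = 20%, g = 50%: (0.35 − 0.10)/0.80 = 0.3125, or −3.8 points.

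**Effect on the test.** This is an exact binomial enumeration of an unadjusted two-sided Wald test on the log odds ratio, with 59 controls and 59×(1 − f) retained HDT15 patients. Site and NIHSS stratum are not modelled. With no exclusion, the chance of a significant result favouring HDT15 is 2.3%.

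| f | g | Shift (points) | Significant in favour of HDT15 |
|---|---|---|---|
| 10% | 10% | +2.8 | 5.5% |
| 10% | 20% | +1.7 | 4.2% |
| 20% | 10% | +6.3 | 9.4% |
| 20% | 20% | +3.7 | 5.7% |
| 20% | 35% | 0 | 2.5% |
| 20% | 50% | −3.8 | 0.9% |

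**When HDT15 works.** Take a true gain of 20 points in adherent patients, none in the others, f = 20%, and g = 10%. The exclusion analysis targets 41.25 + 20 − 35 = 26.25 points. The full randomised contrast is 0.80 × 20 = 16 points. Dividing by the adherent share gives 16/0.80 = 20 points, the true value in adherent patients.

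**Limit of that alternative.** Division by the adherent share is correct only if tilt below 50% does nothing. If shorter tilt gives half the gain, the contrast is 0.80×20 + 0.20×10 = 18 points and the estimate is 18/0.80 = 22.5. If it gives the full gain, the estimate is 20/0.80 = 25.

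**The case against.** A reader might infer that item (3) necessarily favours HDT15 because patients are removed for reasons tied to outcome. The protocol does not support that. The rule is by duration and is neutral as to reason, so a late start or transfer logistics also count. No section links short tilting to collateral grade. Section 4.2 concerns NIHSS at presentation, not vomiting, discomfort or worsening during the tilt. A shift towards HDT15 is likely if tilt is stopped for events such as neurological worsening that go with poor collaterals, but it is zero or reversed in other cases.

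The removed share may also be small. The listed stopping reasons cover tilting to the end of thrombectomy, whereas item (3) counts only the time up to the angiographic reading, which section 6.1.1 expects 30 to 90 minutes after the start. The exclusions in section 5.2 (vomiting at onset, reduced consciousness, low oxygen saturation, severe heart failure) should reduce early stops further.

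Item (3) is one of four sensitivity analyses and carries no decision rule. The time-weighted analysis already handles adherence without deleting anyone, and the reasons for discontinuation will be reported.

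These points stand. They limit the likely size and leave the direction open. They do not restore comparability: an analysis with bias of unknown sign and size is still no robustness check. Nor does the time-weighted analysis settle the matter, because exposure actually received is not randomised either.

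**Conclusion.** The point holds as a matter of design. Item (3) is a one-arm, post-randomisation exclusion, and its comparison is not protected by randomisation. As written, it cannot show whether the mITT result is robust.

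The bias could run either way. Under no effect, it lies between about −3.8 and +6.3 points for an assumed 10% to 20% removed with a good-collateral rate of 10% to 50%. It is zero when removed patients are typical of their arm. These figures rest on assumed shares and rates and on an unadjusted comparison. The primary mITT analysis and the sample size are unaffected. What is at risk is the interpretation placed on item (3) beside the primary result.

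**What to change.** Replace item (3) in section 9.3.2, and in the statistical analysis plan, with an adherence analysis that keeps all mITT patients in their randomised arms. Estimate the complier average causal effect of tilt for at least 50% of the randomisation-to-angiogram time, with allocation as the instrument. Since section 6.2.1 keeps controls at 0° or above, this is the between-arm risk difference in good collaterals divided by the share of HDT15 patients meeting the 50% rule, with a bootstrap or delta-method interval.

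State the assumption that tilt below 50% has no effect, and show results under partial effect and at other thresholds, because the estimate is too large if shorter tilt works.

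If the exclusion version is kept, label it exploratory rather than a sensitivity analysis of the primary result, and report the baseline collateral status and NIHSS of the removed patients.

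The cost is a short text change. The data are those that item (3) and the time-weighted analysis already need. Section 7.3.2 states that the degree of tilt is recorded; recording of duration is implied by those analyses and is worth confirming in the case report form. The downsides are a wider interval, an added assumption, and no independent test of the null beyond the mITT comparison.
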